#### Data collection and data management

Data from the participating GPs will be collected immediately after recruitment, after participation in the training, during implementation of the GESCO intervention in patient care, and after completing the intervention for all study patients (Table 1).

After recruitment, GPs will complete a written questionnaire on practice characteristics, sociodemographic characteristics, and gender awareness (Nijmegen Gender Awareness in Medicine Scale N-GAMS [50, 51]).

After participation in the educational sessions, GPs will provide written feedback regarding the sessions’ content, the materials used, the acceptability of the intervention within their practice, and their self-efficacy to apply the intervention in patient care. Also, the practices’ Organizational Readiness for Implementing Change will be assessed using the validated ORIC questionnaire [51, 52].

When implementing the intervention in CNCP care, GPs will complete a documentation sheet for each patient consultation which assesses the duration, main contents and results of the consultation, the interventional elements applied, and the GPs personal impression of the consultation. These quantitative data will be manually entered into an electronic data capture system.

For data collections with GPs that will be conducted after completing the intervention for all study patients, qualitative and quantitative methods will be applied. Immediately after finishing two consultations per study patient, a semi-structured telephone interview will be conducted with each GP (Supplementary Material 3). These interviews will be audio-recorded and transcribed afterwards. During transcription, data will be pseudonymized using a unique identification number per GP in order to link the interview data to the quantitative data assessed per physician. Accompanying the interview, the Normalization Process Theory Measure (G-NoMAD) [53, 54] will be obtained to assess the implementation process. Simultaneously with the last patient-out per practice, each GP will complete a questionnaire on sustainability aspects, which will again include the G-NoMAD [53].

In addition to the feasibility aspects assessed from the GPs, aspects on the methods’ feasibility related to the recruitment process and the implementation will be documented by the study team in order to prepare a future larger effectiveness trial (Table 1).

For patients, data will be collected three times: after enrollment (baseline, t0), about 2 months later (immediately after completing the intervention, t1), and 5 months after baseline (t2) (Table 2). All data for the patient-centered pre-post comparison, including self-reported prescribed and over-the-counter medication, will be collected from the patients via phone at baseline and after 5 months. To describe the study population sociodemographic data, gender-related variables for health research (GVHR [55], German translation by study group), and experience of social support (Oslo Social Support Scale OSSS-3 [56, 57]) will be collected at baseline. This procedure will be facilitated by a study nurse who will enter the data directly into an electronic data capture system. The data collection at 2 months will consist of a qualitative, semi-structured telephone interview and will focus on feasibility outcomes (Supplementary Material 4). In detail, the open-ended questions will address the patients’ experience with the intervention and their study participation. This includes their satisfaction with the intervention, their acceptability of the intervention, especially regarding the gender approach, and how they perceived the communication with their GP, with the study center and the data collection process. In addition to qualitative, open-ended questions, any changes in medication use since baseline will be assessed. The interview part on patients’ experiences will be audio-recorded and transcribed verbatim, whereas the data on medications will be entered directly into the electronic data capture system. Qualitative interview data will be pseudonymized using a unique identification number per patient in order to link the interview data to the quantitative data assessed for the pre-post comparison. Additionally, GPs will complete a documentation sheet for each participating patient at baseline and after 5 months, providing information on chronic diseases and prescribed medication. Medication use will be analyzed after Anatomical Therapeutic Chemical coding and in consideration of drug dosages and frequency of administration.

#### Data analysis

Analyses of the qualitative data will be performed in MAXQDA 2022 [68] using a deductive-inductive approach. To this end, deductive categories will first be defined on the basis of the interview guides. Afterwards, the coding schemes will be continuously developed and refined over time by identifying categories directly from the text material. The coding process will be responsibly managed by two researchers and will include coding sessions with a group of researchers from the GESCO study team, GP representatives, and patient representatives with CNCP.

For quantitative data, descriptive statistics will be performed using IBM SPSS Statistics for Windows [69] in order to measure preliminary effects. Patients’ baseline and follow-up data will be compared by applying a *t*-test for dependent samples, the Wilcoxon test or McNemar’s/the sign test depending on the distribution of the outcome variable. The nominal significance level for analyses will be defined as *p* < 0.05. In addition, confidence intervals will be reported for any quantities estimated.

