#### Sample size and recruitment

Ten GPs from different general practices will be recruited for the feasibility study, excluding those practices and GPs that already participated in the development process. Again, GPs will be informed about the study and invited to participate during training sessions at the university and via email distributed to the institutes’ teaching and research practice network. Considering a patient drop-out rate of 20% and a target sample size of 40 patients for the analysis, each of the ten GPs will recruit five patients fulfilling the eligibility criteria defined for the study. This sample size is sufficient to detect, e.g., a mean difference (before and after intervention) of 0.5 on the 10-point-pain scale with a standard deviation of 1 (alpha = 0.05, power = 80%, 2-sided one-sample-*t*-test).

In order to ensure that the patients recruited for the feasibility study will match the eligibility criteria, study team will provide the GPs comprehensive written information and guidelines on how to conduct the feasibility study. To assess fidelity to the protocol, the study team will conduct study monitoring by periodic checks and also provide ongoing support to the GPs, ensuring they understand and adhere to the established procedures. This monitoring will help maintain consistency and compliance throughout the study.

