## Discussion

The GESCO study will examine how the diversity of the experience and processing of pain in patients on LTOT of differing sex and gender can be addressed appropriately and in a quality-enhancing manner in the therapeutic setting. As a result, it will provide a novel personalized concept for the care of patients with CNCP, integrated into preliminary analyses and a subsequent feasibility assessment to ascertain the suitability and implementability of the intervention. It will also be used to pilot the study instruments and measures. Our results regarding the implementation measures will be evaluated to determine the suitability of the intervention for transfer to an efficacy trial. If necessary, the intervention will be adapted or (in the worst case) rejected. The progression criteria, as outlined by Thabane and Lancaster [41] and suggested by Pearson et al. [38], will be used to guide this assessment. The limited sample size of the GESCO study restricts the generalizability of possible interventional effects but the results of this study build a foundation to estimate the sample size for a subsequent cluster randomized controlled trial taking into account the standard deviation. Additionally our estimation will be complemented by other studies from the literature applying the same outcome measures.

By considering sex and gender differences in health care and proposing a sex- and gender-sensitive care concept, the GESCO study team is doing pioneering work, which might also be transferable to other health care scenarios and thereby help improve disease management.

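### The pre-post tests, their confidence intervals and the power statement treat 40 patients nested in ten intervention-delivering GPs as independent, so stated precision is too high if change correlates within GP

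*Protocol article*

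**What the plan says.** All references are to Phase II of the protocol article.

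- **Structure** (*Sample size and recruitment*): "Ten GPs from different general practices will be recruited for the feasibility study", and "each of the ten GPs will recruit five patients fulfilling the eligibility criteria defined for the study". The target is 40 analysed patients after 20% drop-out, about four per GP.
- **Delivery** (*Implementation*, *Intervention*): the GPs are the ones trained. Each holds both counselling sessions with his or her own patients and decides which content to use.
- **Power** (*Sample size and recruitment*): "This sample size is sufficient to detect, e.g., a mean difference (before and after intervention) of 0.5 on the 10-point-pain scale", with SD 1, two-sided alpha 0.05, 80% power and a one-sample t-test.
- **Analysis** (*Data analysis*): patients' "baseline and follow-up data will be compared by applying a" t-test for paired data, a Wilcoxon test, or McNemar's or the sign test, chosen by the outcome's distribution. The nominal level is 0.05, and every estimate gets a confidence interval.
- **Use of the results** (*Discussion*): they are to help size "a subsequent cluster randomized controlled trial taking into account the standard deviation".

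No ICC, design effect, random GP effect or cluster-robust standard error is mentioned.

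**The concern.** Patients of one GP share that GP's skill, fidelity to the training and choice of content. These act on the change from baseline, so taking pre-post differences does not remove them. Differencing removes only stable level differences between practices.

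The named tests and the one-sample power calculation ignore any such correlation. Because the tests are named, this is a method the protocol fixes, not a detail left to an unseen analysis plan.

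What is at stake is the stated precision of the preliminary effects. In an exploratory study the confidence interval is the main quantitative product, and here the clinical parameters are a co-primary aim. The results are also meant to help size a cluster randomised trial. Such a trial needs an ICC as well as a standard deviation, and no ICC estimate is planned.

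**Working it through.** **Inputs.** From *Sample size and recruitment*: k = 10 GPs, 5 recruited per GP, 20% drop-out, 40 analysed (m = 4 per GP), mean change 0.5, SD 1, two-sided alpha 0.05. The SD is read as that of the change, since a one-sample test is named. The ICC of change is not in the document; 0 to 0.20 is assumed.

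**1. The protocol's own figure.** Recruitment: 40 / (1 − 0.20) = 50 = 10 × 5, as stated. Power of the one-sample t-test (noncentral t, noncentrality 0.5 × √n): n = 33 gives 79.5%, n = 34 gives 80.8%, n = 40 gives 86.9%. So 40 is enough under independence, with six patients to spare.

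**2. Allowing for clustering.**
- Design effect: DE = 1 + (m − 1) × ICC = 1 + 3 × ICC.
- Effective sample size: 40 / DE.
- Type I error of the planned t-test: the true variance of the mean is DE/40, while the expected sample variance is (40 − DE)/39. The t statistic is therefore inflated by r = √[DE × 39/(40 − DE)], and the error rate is 2 × P(t39 > 2.023/r). At ICC 0.10: DE = 1.30, r = √(1.30 × 39/38.7) = 1.145, 2.023/1.145 = 1.767, giving 8.5%.
- Power: noncentral t with noncentrality 0.5 × √(40/DE), on 39 df (design effect only) or 9 df (ten GP means).

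| ICC (assumed) | DE | Effective n | Type I error, formula | Type I error, simulated | Widening, √DE | Power, 39 df | Power, 9 df |
|---|---|---|---|---|---|---|---|
| 0 | 1.00 | 40.0 | 5.0% | 4.9% | none | 86.9% | 80.3% |
| 0.01 | 1.03 | 38.8 | 5.3% | 5.4% | 1.5% | 86% | 79% |
| 0.05 | 1.15 | 34.8 | 6.7% | 6.5% | 7% | 82% | 75% |
| 0.10 | 1.30 | 30.8 | 8.5% | 8.5% | 14% | 77% | 70% |
| 0.20 | 1.60 | 25.0 | 12.1% | 12.0% | 26% | 68% | 61% |

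The simulated column comes from 50,000 trials of 10 × 4 per setting. Separate simulations gave 6.6% at ICC 0.05, the value used in the text. In the same runs a t-test on the ten GP means stayed at 4.7% to 5.0%.

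**3. Splitting the interval width.** With SD 1 the planned 95% half-width is 2.023/√40 = 0.320. On 9 df at ICC 0 it is 2.262/√40 = 0.358, already 12% wider. At ICC 0.05 it is 0.358 × √1.15 = 0.384 (20% wider), and at 0.10 it is 0.358 × √1.30 = 0.408 (28% wider). So about 12% is the price of using ten GP means; the rest (7% and 14%) is clustering.

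**4. Where 80% power is lost.** On sample size inflation alone: (40/34 − 1)/3 = 0.059. By noncentral t on 39 df: ICC of about 0.07. On 9 df: ICC of about 0.003.

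**5. Which model helps.** Random GP and patient intercepts were fitted to the repeated measurements in 300 simulated 10 × 4 trials with an ICC of change of 0.20. The standard error of the time effect equalled that of the paired t-test (median ratio 1.000), and both rejected in 13%. The GP effect must therefore act on the change.

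**The case against.** The strongest defence is the study's purpose. It is a single-arm, exploratory feasibility study with a nominal significance level. Transfer to a larger trial is judged on implementation measures and progression criteria, and effect and sample size estimates will also draw on other studies. No stated decision turns on p < 0.05, and in the planned 10 × 4 layout clustering does not bias the estimated mean change. All of this stands. It lowers the urgency but does not make the intervals right.

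The size is also uncertain. Differencing removes stable practice differences, and the ICC of change may be small; at 0.01 the error rate is only about 5.3%. That stands too, so the harm must be stated as conditional.

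Three stronger readings are tempting, and the protocol does not support them.

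- A reader might infer that the intervals are certainly too narrow. At ICC 0 the planned tests are valid, and no ICC is given.
- A reader might infer that the power claim is wrong, or holds only with almost no GP effect. It is correct for the test it names, and on the design effect alone it survives to an ICC of about 0.06 to 0.07. It gives way almost at once only under a 9-df analysis.
- A reader might infer that the authors recognise clustering here and ignore it. The *Discussion* describes the design of a later trial and says nothing about correlation in this one.

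Finally, an ICC from ten GPs with four patients each is very imprecise. At a true ICC of 0.05 the moment estimate of the GP variance is zero or negative in about 40% of trials. That is a reason to report it with its interval and not rely on it alone.

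**Conclusion.** The point holds in conditional form and should be fixed. The named tests, their confidence intervals and the power statement assume 40 independent patients, in a design where ten GPs deliver the intervention to their own patients. For any positive ICC of change the intervals are too narrow and the 5% level is exceeded. The excess is slight at 0.01; at 0.05 to 0.10 the error rate is 6.6% to 8.5% and the design effect alone calls for intervals 7% to 14% wider; at 0.20 the error rate is about 12% and the widening 26%.

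These figures assume an equal four patients per GP, normally distributed changes and an ICC range that is not from the protocol. They were computed for the t-test. The Wilcoxon, McNemar and sign tests rest on the same independence assumption but were not simulated.

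The sufficiency of 40 patients is not an arithmetic error. It depends on independence, which the protocol does not say.

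**What to change.** 1. **Continuous outcomes.** Analyse change scores at GP level, either by a t-test on the ten GP mean changes (9 df) or by a mixed model on the change score with a random GP intercept and small-sample degrees of freedom. In a repeated-measures model the equivalent is a random GP-by-time effect; random intercepts alone do not solve the problem.
2. **Binary outcomes.** Replace McNemar's and the sign test by cluster methods with a small-sample correction.
3. **ICC.** Report the ICC of change with its interval, which will be wide, as one input to the planned cluster trial alongside external values.
4. **Power sentence.** State that 40 patients give 86.9% power if patients are independent (34 would give 80.8%). With a GP-level analysis on 9 df, power is about 80% at ICC 0, 75% at 0.05 and 70% at 0.10.

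Cost: changed wording, a less favourable power figure and wider intervals, including about 12% from the loss of degrees of freedom even if the ICC is zero. No extra patients are needed. The change should be made before outcome data are analysed, so that it does not look data-driven.

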### Patient and public involvement

The realization of the GESCO study is accompanied by a multi-perspective advisory board that includes female and male patient representatives, but also experts in general practice, pain medicine, addiction medicine, psychology, health care education, sociology, gender research, and participatory research. The advisory board members will be informed about the study process and asked for advice in regular meetings. In addition to these meetings, they will get actively involved into the following activities:Development of the intervention and its implementation strategy within primary carePreparation of the feasibility study including the development and pre-testing of study material for patients and GPs, interview guidelines, and questionnaireRecruitment of interview partners for the needs assessments and recruitment of primary care practices for the feasibility studyThe discussion and dissemination of results including contribution to conference presentations and to scientific or low-threshold, generally understandable publications (e.g., flyers or brochures)

In order to adequately consider the perspective of potential addressees of the GESCO intervention during the whole study, researchers working in the project planned and reflected involvement activities, which especially affect patient representatives and GPs, together with these stakeholders. For this, they used the so-called involvement matrix [70]. This process was already carried out prior to the beginning of phase I and was facilitated by an advisory board member familiar with applying the involvement matrix. It aimed to enable everyone to specify how intensively and in which project phases they would like to get involved or not to get involved.

## Ethics and dissemination

### Ethics approval

The study obtained ethical approval from the Ethics Commission of Witten/Herdecke University (reference number: 138/2022, date of approval: 08/25/2022, amendment: 08/29/2023).

### Dissemination policy

As is customary, it is planned to publish a description of the intervention components and the results of the pilot testing in international journals and to present all results at scientific conferences. In order to also make the study results transparent and comprehensible for the non-scientific public, a GESCO symposium addressing GPs, patients, researchers, and the public will be conducted at the end of the project. For this, the study conduct and its results will be prepared in simple language, which will be facilitated by patient representatives, GPs, and other members of the GESCO advisory board. Beside the public symposium, it is planned to disseminate the results at a low threshold level, i.e., via magazines of self-help organizations. The dissemination strategy will be planned together with patient representatives and GPs.

The dissemination policy will also include an analysis of whether the sex- and gender-sensitive concept developed for CNCP management might be transferable to other health care scenarios.

As the project is part of a larger funding initiative of the German Federal Ministry of Health, which aims to investigate and establish gender equality in health, information on the GESCO project and its results will also be published on the ministry’s website.

## Discussion

The GESCO study will examine how the diversity of the experience and processing of pain in patients on LTOT of differing sex and gender can be addressed appropriately and in a quality-enhancing manner in the therapeutic setting. As a result, it will provide a novel personalized concept for the care of patients with CNCP, integrated into preliminary analyses and a subsequent feasibility assessment to ascertain the suitability and implementability of the intervention. It will also be used to pilot the study instruments and measures. Our results regarding the implementation measures will be evaluated to determine the suitability of the intervention for transfer to an efficacy trial. If necessary, the intervention will be adapted or (in the worst case) rejected. The progression criteria, as outlined by Thabane and Lancaster [41] and suggested by Pearson et al. [38], will be used to guide this assessment. The limited sample size of the GESCO study restricts the generalizability of possible interventional effects but the results of this study build a foundation to estimate the sample size for a subsequent cluster randomized controlled trial taking into account the standard deviation. Additionally our estimation will be complemented by other studies from the literature applying the same outcome measures.

By considering sex and gender differences in health care and proposing a sex- and gender-sensitive care concept, the GESCO study team is doing pioneering work, which might also be transferable to other health care scenarios and thereby help improve disease management.

## Data Availability

Not applicable.

## Abbreviations

CNCP: Chronic non-cancer pain
DASS: Depression-Anxiety-Stress Scale
FW7: The Marburg questionnaire on habitual well-being
GESCO: Gender-sensitive care for chronic non-cancer pain patients receiving long-term opioid therapy
GVHR: Gender-related variables for health research
GP: General practitioner
ISCP: Internalized Stigma of Chronic Pain
LTOT: Long-term opioid therapy
MRC: UK Medical Research Council
N-GAMS: Nijmegen Gender Awareness in Medicine Scale
NoMAD: Normalization Process Theory Measure
ORIC: Organizational Readiness for Implementing Change
OSSS-3: Oslo Social Support Scale
PDI: Pain Disability Index
PMQ: Pain Medication Questionnaire
SIMS: Satisfaction with Information about Medicines Scale
SOP2: Optimism-Pessimism Short Scale-2
VR-12: Veterans RAND 12-Item Health Survey
